4.3 Blinding

This is an open-label study; neither investigators nor participants are blinded to treatment allocation.

However, laboratory personnel responsible for SARS-CoV-2 testing and antibody titer quantification are blinded to treatment assignment to minimize analytical bias. Clinical investigators and patients were aware of group assignment solely for safety monitoring and transfusion logistics.

4.4 Intervention

4.4.1 Experimental Group (CCP Group)

Participants receive standard supportive care plus four infusions of high-titer COVID-19 convalescent plasma (CCP).

Dosage: 200 mL per infusion.

Infusion schedule:

1. Day +14 ± 2 days
2. Day +28 ± 2 days
3. ~2 months (±7 days)
4. ~3 months (±7 days)

Each CCP unit must meet the following criteria:

Collected from donors who have fully recovered from COVID-19 and are at least 14 days symptom-free.

Confirmed SARS-CoV-2 PCR negative at the time of donation.

Tested positive for anti–SARS-CoV-2 IgG with high antibody titer (S/CO ≥ 12) according to ELISA testing standards.

ABO compatible with the recipient.

Infusions are administered intravenously at a rate not exceeding 2 mL/kg/hour, with continuous monitoring for transfusion reactions.

4.4.2 Control Group

Participants in the control arm receive standard supportive care according to institutional post-HSCT guidelines, without plasma infusion.

4.5 Concomitant Medications and Standard Supportive Care

Both study arms follow the same post-HSCT standard of care, including:

Antimicrobial prophylaxis (bacterial, viral, and fungal).

GVHD prophylaxis (e.g., calcineurin inhibitors, methotrexate, or mycophenolate mofetil).

Blood component support (platelets, red blood cells) as clinically indicated.

Ursodeoxycholic acid (UDCA) is permitted as part of the institutional hepatoprotective regimen and is used equally in both groups; it is not considered a study intervention.

4.6 Safety Monitoring

All adverse events (AEs) and serious adverse events (SAEs) occurring during or after CCP infusion will be recorded.

Events are graded according to Common Terminology Criteria for Adverse Events (CTCAE) version 5.0, categorized by severity (Grade 1–5) and relationship to the study intervention (definite, probable, possible, unrelated).

All SAEs are reported within 24 hours to the principal investigator and reviewed by the institutional ethics committee.

An independent Data and Safety Monitoring Board (DSMB) oversees trial conduct and safety data.

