**Secondary Endpoints:**

1. Incidence and severity of COVID-19 (mild/moderate/severe).
2. Overall survival (OS) at one year.
3. Time to first SARS-CoV-2 infection.
4. Incidence of adverse events related to plasma infusion.
5. SARS-CoV-2 antibody titers and their kinetics over time.

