3.2 Secondary Objectives

1. To assess the severity and clinical course of COVID-19 infection (mild, moderate, severe, or critical) in CCP versus control groups.

2. To evaluate overall survival (OS) at one year post-transplant.

3. To determine the time to first SARS-CoV-2 infection after transplantation.

4. To assess the kinetics and durability of anti–SARS-CoV-2 antibody levels following CCP infusion.

5. To evaluate the safety and tolerability of CCP administration by recording infusion-related and systemic adverse events.

6. To explore correlations between antibody titers and clinical outcomes.

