3.4 Secondary Endpoints

1. COVID-19 severity grading according to WHO Clinical Progression Scale (scores 1–10).

2. Overall survival rate at 12 months post-transplant.

3. Time to first COVID-19 diagnosis (days from transplantation to first positive test).

4. Quantitative or semiquantitative SARS-CoV-2 antibody titers measured at predefined intervals (baseline, pre-infusion, and 14, 28, 60, 90, 180, and 365 days post-transplant).

5. Number and proportion of adverse events (AEs) and serious adverse events (SAEs) related to plasma infusion, graded according to CTCAE v5.0.

6. Association between CCP antibody titer and risk reduction for COVID-19 infection or severe disease.

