4.7 Follow-Up and Assessments

| **Time Point** | **Clinical Assessments** | **Laboratory Assessments** |
| --- | --- | --- |
| Baseline (pre-transplant) | Demographics, medical history, HSCT details, donor type | SARS-CoV-2 antibody titer, PCR test |
| Day +14 | Vital signs, infusion tolerance | Antibody titer, CBC, liver/renal function |
| Day +28 | AE assessment, infection monitoring | Antibody titer, PCR test |
| 2 months | Clinical evaluation, GVHD status | Antibody titer, PCR test |
| 3 months | Clinical evaluation | Antibody titer, PCR test |
| 6 months | Infection and survival status | Antibody titer |
| 12 months | Final follow-up | Antibody titer, survival status |

COVID-19 infection is defined as PCR-confirmed SARS-CoV-2 positivity by nasopharyngeal swab or other approved method.

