5.2 Analysis Populations

Three analysis populations will be defined:

1. Intention-to-Treat (ITT) population:

Includes all randomized participants, analyzed according to the group to which they were originally assigned, regardless of treatment received.

2. Per-Protocol (PP) population:

Includes participants who complete all planned study procedures and at least four CCP infusions (for the CCP arm) without major protocol violations.

3. Safety population:

Includes all participants who receive at least one CCP infusion (in the experimental group) or standard care (in the control group), used for safety analyses.

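### The adverse-event recording rule gives controls no collection window, and the safety endpoint cannot be compared between arms even if their events are recorded

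*Protocol*

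**What the plan says.** Section 4.6 (Safety Monitoring) gives the recording rule: "All adverse events (AEs) and serious adverse events (SAEs) occurring during or after CCP infusion will be recorded". Section 4.4.2 describes the comparator: "Participants in the control arm receive standard supportive care according to institutional post-HSCT guidelines, without plasma infusion". Section 5.2 sets out who enters the safety tables: "Includes all participants who receive at least one CCP infusion (in the experimental group) or standard care (in the control group), used for safety analyses".

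The safety objective in section 3.2 is broad: "To evaluate the safety and tolerability of CCP administration by recording infusion-related and systemic adverse events". The matching endpoint in section 3.4 is narrower: "Number and proportion of adverse events (AEs) and serious adverse events (SAEs) related to plasma infusion, graded according to CTCAE v5.0". The synopsis endpoint is equally narrow: "Incidence of adverse events related to plasma infusion".

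Three other places bear on scope. Section 4.1 commits to following participants, without distinction by arm, for safety events over the whole observation period. The synopsis paragraph on safety monitoring grades and summarises adverse events, again without naming an arm. The visit table in section 4.7 names adverse-event assessment in one row, Day +28: "AE assessment, infection monitoring". Section 4.3 states that the trial is open-label, with blinding confined to laboratory staff.

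**The concern.** The start of recording is tied to an exposure that one arm never has. A site that follows section 4.6 literally would open adverse-event pages for plasma recipients from their first infusion and would have no defined point at which to open them for controls. An analyst who follows section 5.2 would then tabulate controls whose events nobody was told to collect. An analysis plan cannot repair this later, because events that were not entered cannot be analysed.

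The endpoint adds a second problem. After allogeneic transplantation, fever, respiratory events and infections occur without plasma. Telling an excess from that background needs a concurrent rate, and the randomised control arm could supply it. An endpoint restricted to plasma-related events leaves the control arm out and relies on causality judgements by investigators who know the allocation.

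Oversight is affected too. The interim safety review in section 5.5 is triggered by 20 participants completing their infusions, and section 6.3 routes to the DSMB those SAEs suspected to be related to plasma. Without a control rate, the board has little against which to judge a non-specific signal.

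**Working it through.** The protocol states no safety figure to reproduce. The check is mainly a comparison of texts, followed by a short illustration of precision.

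**Step 1: who is covered by which statement.**

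| Protocol section | Plasma arm | Control arm |
| --- | --- | --- |
| 4.6, recording rule | From first infusion | No window defined |
| 4.1, follow-up | Safety events, whole period | Safety events, whole period |
| 4.7, visit table | AE assessment named at Day +28 only | AE assessment named at Day +28 only |
| 5.2, safety population | Included | Included |
| 3.4 and synopsis, safety endpoint | Plasma-related events | None possible by definition |

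Sections 4.1 and 5.2 expect control-arm safety data, and section 4.6 gives no rule that produces them. Section 4.6 also leaves out plasma-arm events between randomisation and the first infusion. If sites opened control recording at randomisation on their own initiative, the two windows would still differ.

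**Step 2: does the visit table close the gap?** Only at one visit. Day +14 lists infusion tolerance, which has meaning only in the plasma arm. The 2-, 3-, 6- and 12-month rows do not name adverse-event assessment, although the third and fourth infusions fall at about 2 and 3 months (section 4.4.1).

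**Step 3: does full recording in controls rescue the endpoint?** No. A patient who receives no plasma cannot have a plasma-related event, so the control count is zero whatever is recorded. The difference between arms would then simply equal the plasma-arm count of events called related.

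**Step 4: what a common rule would buy.** Inputs: 36 per arm (section 5.1) and a background proportion p for a given event type. The protocol does not give p, so 30%, 50% and 70% are assumptions. The 95% half-width of the between-arm difference, with equal true rates, is 1.96 × √(2p(1−p)/36).

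- p = 30%: 1.96 × √(0.42/36) = 21.2 points
- p = 50%: 1.96 × √(0.50/36) = 23.1 points
- p = 70%: 1.96 × √(0.42/36) = 21.2 points

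The plasma-arm proportion detectable with 80% power (two-sided 5% comparison of two proportions) is about 62%, 81% and 95% respectively.

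**Step 5: what the plasma arm alone gives.** At p = 30%, about 11 of 36 plasma recipients (0.30 × 36 = 10.8) would have the event with no plasma effect at all. The exact 95% interval for 11/36 is 16% to 48%, with no control rate to set beside it. For an acute reaction tied in time to infusion, the plasma arm is informative by itself: zero events in 36 gives a one-sided 95% upper bound of 1 − 0.05^(1/36) = 8.0%.

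**The case against.** A reader might infer that adverse events are recorded exclusively in plasma recipients, that the control arm therefore has no safety data, and that the safety aim cannot be met. The documents do not support that reading, for four reasons.

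- Section 4.6 does not say that other events go unrecorded.
- Section 4.1, the synopsis and the Day +28 row are not restricted by arm, and including controls in the safety population is itself evidence that their data are intended.
- One-year survival, infection and COVID-19 severity are outcomes in both arms, and GVHD status is scheduled at 2 months. Death, the hardest safety outcome, is therefore compared as randomised.
- The main risks named in section 6.3 are allergic and febrile reactions and TRALI, which are close in time to infusion and can be assessed without a control group. Section 4.6 also has an unrelated category, so recording after infusion in the plasma arm covers all causes.

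All of this stands, and it limits the point. It does not remove it. The statements that imply wider collection express intentions. The one operative recording rule does not carry them out, and the visit table does so at a single visit. None of them alters an endpoint that is empty in the control arm by construction.

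It is also fair to say that 36 per arm would not separate a moderate excess from background even with equal recording. That argues against expecting much from the comparison, but not for leaving it out: an interval of about ±21 points is still a randomised estimate, and the present endpoint gives none.

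**Conclusion.** The point holds as an internal contradiction together with a badly fixed endpoint. Section 4.6 gives controls no recording window, contrary to sections 4.1 and 5.2. The plasma-related endpoint in section 3.4 and the synopsis cannot be compared between arms under any reading, and attribution rests on unblinded judgement.

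The consequence is confined to delayed and non-specific systemic events. These fall within the objective in section 3.2, and a concurrent control rate is what makes them interpretable. Survival, infection and the assessment of acute infusion reactions are not undermined, and the primary endpoint is unaffected. To say that controls have no safety data at all would go beyond the text.

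The conclusion on the wording rests on no assumed number. The precision figures do: half-widths of 21 to 23 points assume background rates of 30 to 70%, equal true rates in the arms and all 36 per arm contributing.

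**What to change.** 1. Reword section 4.6 so that all AEs and SAEs are recorded in both arms from randomisation, over the same window and with the same elicitation. This brings it into line with sections 4.1 and 5.2.
2. Add adverse-event assessment, for both arms, to the existing visits in the section 4.7 table.
3. In section 3.4 and the synopsis, add as a safety endpoint the between-arm comparison of all-cause Grade 3 or higher AEs and of SAEs, reported as a difference with a 95% CI.
4. Keep infusion-related reactions, with their causality grading, as a descriptive table for the plasma arm only.

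The cost is protocol wording and extra CRF entries for about 36 controls at visits that already take place. This is some added work, since most of those visits do not currently name adverse-event assessment, but it needs no new visit or procedure. The new comparison should be presented as estimation: at this sample size it can show large excesses and bound the rest only loosely.

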4.7 Follow-Up and Assessments

| **Time Point** | **Clinical Assessments** | **Laboratory Assessments** |
| --- | --- | --- |
| Baseline (pre-transplant) | Demographics, medical history, HSCT details, donor type | SARS-CoV-2 antibody titer, PCR test |
| Day +14 | Vital signs, infusion tolerance | Antibody titer, CBC, liver/renal function |
| Day +28 | AE assessment, infection monitoring | Antibody titer, PCR test |
| 2 months | Clinical evaluation, GVHD status | Antibody titer, PCR test |
| 3 months | Clinical evaluation | Antibody titer, PCR test |
| 6 months | Infection and survival status | Antibody titer |
| 12 months | Final follow-up | Antibody titer, survival status |

COVID-19 infection is defined as PCR-confirmed SARS-CoV-2 positivity by nasopharyngeal swab or other approved method.

4.8 Data Collection and Quality Control

All data are recorded in case report forms (CRFs) and entered into a secure electronic database.

Double data entry and periodic quality audits are conducted by independent monitors.

Any protocol deviations or missing data are documented and reported.

**Ⅴ. Statistical Considerations**

5.1 Sample Size Determination

The sample size was calculated based on the expected difference in the incidence of COVID-19 infection between the CCP group and the control group.

According to preliminary clinical observations and published data, the infection rate within one year after HSCT was estimated at 80% in the control group and 50% in the CCP group.

Assuming a two-sided significance level (α = 0.05) and a statistical power of (1 – β = 0.80), and using a log-rank test for comparison between groups, the required total sample size was calculated to be 72 participants (36 per group).

This number also accounts for an estimated 10% attrition rate due to loss to follow-up or early withdrawal.

The sample-size calculation was performed using PASS software version 15.0 (NCSS, Kaysville, UT, USA).

5.2 Analysis Populations

Three analysis populations will be defined:

1. Intention-to-Treat (ITT) population:

Includes all randomized participants, analyzed according to the group to which they were originally assigned, regardless of treatment received.

2. Per-Protocol (PP) population:

Includes participants who complete all planned study procedures and at least four CCP infusions (for the CCP arm) without major protocol violations.

3. Safety population:

Includes all participants who receive at least one CCP infusion (in the experimental group) or standard care (in the control group), used for safety analyses.

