**Statistical Analysis:**

Both intention-to-treat (ITT) and per-protocol (PP) analyses will be performed. Kaplan–Meier survival curves will be generated, and group comparisons will use the log-rank test. Continuous variables will be compared using the t-test or Mann–Whitney U test; categorical variables using χ² or Fisher’s exact test.

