**Figure 1. Study schedule.**

**Timeline of convalescent plasma (CCP) infusions and virological/immunological monitoring after HSCT. CCP infusions were given on days +14, +28, +60, and +90. Twice-weekly nucleic acid and weekly antibody testing continued through day +120.**

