**Ⅳ. Study Design and Methodology**

4.1 Study Design

This is a prospective, single-center, open-label, randomized controlled trial evaluating the prophylactic efficacy and safety of COVID-19 convalescent plasma (CCP) in adult patients early after allogeneic hematopoietic stem-cell transplantation (HSCT).

Eligible participants are randomized in a 1:1 ratio to receive either:

Experimental group (CCP group): Standard supportive care plus four planned CCP infusions.

Control group: Standard supportive care without CCP.

The total study duration for each participant is 12 months after transplantation. Participants will be followed for clinical outcomes, infection status, and safety events throughout the observation period.

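### The per-protocol rule requires completion of all planned procedures, including a month-12 blood sample, so as written it drops everyone who dies in the first year and fixes any per-protocol one-year survival at 100%

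*Protocol*

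**What the plan says.** Section 5.2 of the protocol defines the PP population: "Includes participants who complete all planned study procedures and at least four CCP infusions (for the CCP arm) without major protocol violations". The parenthesis attaches to the four infusions only, so completion of procedures is required in both arms.

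The planned procedures extend over the whole year:
- Section 4.1: "The total study duration for each participant is 12 months after transplantation".
- Section 3.4 lists antibody titers at "baseline, pre-infusion, and 14, 28, 60, 90, 180, and 365 days post-transplant".
- The last row of the section 4.7 table, at 12 months, reads "Final follow-up | Antibody titer, survival status".
- The Figure 1 caption adds denser early testing: "Twice-weekly nucleic acid and weekly antibody testing continued through day +120".

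One of the secondary endpoints in section 3.4 is "Overall survival rate at 12 months post-transplant". On the use of the populations, the Study Summary states: "Both intention-to-treat (ITT) and per-protocol (PP) analyses will be performed". It names no endpoint to which the PP analysis is limited and none from which it is withheld.

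**The concern.** A PP set should be defined by adherence to the assigned strategy. Here it is defined partly by an outcome. A control participant who dies on day 200, or a plasma recipient who has had all four infusions and dies on day 300, has not given the month-12 sample and so has not completed all planned procedures. Neither has violated the protocol.

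Two results are at stake. A PP survival table would show no deaths in either arm, which a reader could take as evidence of equal survival. The PP infection and severity analyses would lose infections followed by death before month 12, and with them every fatal COVID-19 case in that period. Section 2.1 describes this population as being at exceptionally high risk of severe infection and death, so these cases matter.

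**Working it through.** **Step 1: who can be in the PP set.** Membership requires all planned procedures (section 5.2). These include the month-12/day-365 titer (sections 3.4 and 4.7). Survival status in the same row of section 4.7 can be recorded for someone who has died; the titer cannot be obtained. Hence membership implies being alive at month 12.

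**Step 2: PP survival.** It follows that P(alive at month 12 | in PP) = 1 in each arm, with no assumption about mortality. With no deaths in either arm, the log-rank observed-minus-expected difference and its variance are both zero, so the test cannot be computed.

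**Step 3: how many the rule removes.** The documents give no mortality figure, so one-year survival S is assumed. With 36 per arm (section 5.1), the expected number removed per arm is 36 × (1 − S):

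| Assumed S | Removed, of 36 | PP one-year survival |
| --- | --- | --- |
| 90% | 36 × 0.10 = 3.6 | 100% |
| 80% | 36 × 0.20 = 7.2 | 100% |
| 70% | 36 × 0.30 = 10.8 | 100% |

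An assumed true difference of 60% in control against 90% with plasma would remove 36 × 0.40 = 14.4 and 36 × 0.10 = 3.6 participants, and would still appear as 100% against 100%. A simulation with exponential death times (20,000 replicates, 36 per arm) gave the same picture.

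**Step 4: PP infection incidence.** In one arm, let p be the proportion infected, and let d1 and d0 be the proportions of infected and uninfected participants who die before month 12. Among survivors the odds of infection are [p/(1 − p)] × [(1 − d1)/(1 − d0)]. If infected participants die more often, PP incidence is too low. The odds ratio between arms is also distorted if the second factor differs by arm, for example if plasma changes the fatality of infection. The documents give neither d1 nor d0, so no size can be attached.

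**Step 5: would removing the completion condition be enough?** No, if the four-infusion condition stays unchanged. Plasma participants would still have to survive to about day 90 for the fourth infusion, while controls would not. With exponential deaths, PP survival in the plasma arm would be S^((365 − 90)/365) = S^0.753, against S in control. With equal true survival in the two arms:
- S = 90%: 92% plasma against 90% control.
- S = 80%: 85% against 80%.
- S = 70%: 76% against 70%.

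These gaps are produced by the definition alone.

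**The case against.** Planned procedures are not defined further, and they could be read as those due while the participant is alive. Naming major violations in the same sentence suggests that small lapses were meant to be tolerated, and the SAP, which is not at hand, may say what counts as completion. That reading is possible, but no section states it, and the sentence as it stands gives the other result. A stated rule that produces a wrong set is more than detail left to the SAP. In an open-label trial with 36 per arm, membership should not be left to interpretation.

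Section 5.2 keeps all randomised participants in ITT, and the safety population carries no completion condition. A PP analysis of survival is itself inferred from the general sentence in the Study Summary; no section commits to one by name. These points stand and limit the reach of the concern.

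Four stronger readings are tempting, and the documents do not support them:
- **That a survival benefit or harm of plasma cannot appear in the trial.** ITT survival counts every death.
- **That the PP infection comparison is emptied.** Non-fatal infections in completers remain; the problem is selection.
- **That the PP set shrinks to a handful of perfect attenders.** Literally, one missed scheduled test does exclude a participant. How many that removes cannot be derived: the Figure 1 caption gives no start day, the section 4.7 table lists only seven time points, no rate of missed tests is given, and tests due at the same visit tend to be missed together.
- **That the major-violation condition becomes redundant.** It could still exclude, for instance, an ineligible participant who attended everything.

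**Conclusion.** The point holds for the PP population only. As written, section 5.2 excludes from PP, in both arms, anyone who dies before month 12. Any PP one-year survival result is then 100% in both arms and carries no information, and the PP infection and severity results are conditional on surviving the year. This rests on the literal wording of section 5.2 together with the month-12 titer in sections 3.4 and 4.7, and on no section exempting deaths. The 100% needs no numerical assumption. The numbers removed (3.6 to 10.8 of 36 per arm) rest on assumed survival of 90% to 70%. The size of the bias in PP infection incidence, and the loss through missed tests, cannot be stated from the documents. The ITT results are untouched. The wording should be corrected, but it does not threaten the primary ITT comparison.

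**What to change.** Revise the PP definition in section 5.2 in one edit:

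1. Delete the condition on completing all procedures. Define PP in both arms as randomised participants with no major protocol violation up to the earliest of first infection, death or month 12.
2. State that death, infection, or an isolated missed test or visit is not a violation.
3. For the plasma arm, apply the infusion condition only to infusions scheduled before that earliest date, so that early death or infection does not itself exclude a participant. Without this, the one-sided survivor selection in step 5 remains.
4. State that overall survival is analysed in the ITT population only.

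The cost is a few sentences, with no new participants, visits or data. The downside is a PP set slightly less strict on attendance.

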3.3 Primary Endpoint

Incidence of laboratory-confirmed SARS-CoV-2 infection within 12 months after HSCT.

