6.3 Participant Safety and Risk Management

The primary potential risks involve transfusion-related reactions, including mild allergic reactions, febrile non-hemolytic transfusion reactions, or rare severe complications such as transfusion-related acute lung injury (TRALI).

All CCP infusions are conducted under physician supervision with continuous monitoring of vital signs.

If any Grade ≥3 adverse event occurs, the infusion is immediately discontinued, and appropriate medical management is initiated.

Any serious adverse event (SAE) suspected to be related to CCP infusion will be reported to the Ethics Committee and the Data and Safety Monitoring Board (DSMB) within 24 hours.

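### The per-protocol set demands four infusions to about day +90 in the CCP arm, with no matching time condition in controls, so it favours CCP if infected participants miss infusions

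*Protocol*

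**What the plan says.** Section 5.2 sets the PP population: "Includes participants who complete all planned study procedures and at least four CCP infusions (for the CCP arm) without major protocol violations". The procedures and violations clauses apply to both arms; the infusion count applies to the CCP arm only.

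The Figure 1 caption gives the infusion days: "CCP infusions were given on days +14, +28, +60, and +90". Section 4.4.1 allows 7 days either side of the three-month infusion, so the fourth can fall as late as about day +97. Section 4.4.2 describes the other arm: "Participants in the control arm receive standard supportive care according to institutional post-HSCT guidelines, without plasma infusion".

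The primary endpoint in section 3.3 is "Incidence of laboratory-confirmed SARS-CoV-2 infection within 12 months after HSCT", and section 3.4 measures time to first infection from transplantation. Events before the fourth infusion therefore count.

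On the role of the two analyses, the Study Summary says only "Both intention-to-treat (ITT) and per-protocol (PP) analyses will be performed". Neither is ranked there or in section 5.

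**The concern.** Membership of the CCP arm's PP set depends on what happens to the participant over roughly the first three months of follow-up. Nothing comparable applies to controls. A control infected on day 40 is a PP event. A CCP participant infected on day 40 is a PP event only if the remaining infusions are still given. If they are not, the retained CCP participants carry event-free time that the definition guaranteed them, which is immortal-time bias.

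At stake is the reading of the PP result. In an open-label superiority trial with no stated primary population, a PP benefit could be presented as confirmation of efficacy, or as the main result, when some or all of it comes from the definition.

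**Working it through.** The protocol gives no figure for the PP analysis, so there is none to reproduce. The size of the bias is derived under no true effect.

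**Inputs from the protocol.** 36 per arm, 80% one-year infection in controls, two-sided 5% level and log-rank test (section 5.1); fourth infusion at day 90 (Figure 1 caption).

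**Assumptions not in the protocol.** Constant infection hazard (a front-loaded Weibull hazard, shape 0.6, as a variant); risk counted from day 0 or from day 14; one-year mortality of 0–30%, independent of infection; and q, the share of CCP participants infected before day 90 who miss an infusion.

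**Step 1: who is at risk of exclusion.** λ = −ln(1 − 0.80) = 1.609 per year.
- From day 0: 1 − exp(−1.609 × 90/365) = 1 − exp(−0.397) = 32.8% infected by day 90, or 36 × 0.328 = 11.8 participants.
- From day 14: 1 − exp(−1.609 × 76/365) = 1 − exp(−0.335) = 28.5%.

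**Step 2: PP incidence at q = 1, from day 0, no deaths.** (0.8000 − 0.3276)/(1 − 0.3276) = 0.4724/0.6724 = 70.3% in CCP, against 80% in controls.

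**Step 3: apparent rate ratio at q = 1.** Each retained CCP participant brings guaranteed event-free time a/λ, then infection probability p = 0.7026 over the remaining 275 days with expected time p/λ. The ratio to the control rate λ is p/(a + p).
- From day 0: 0.7026/(0.3968 + 0.7026) = 0.64.
- From day 14: 0.7026/(0.3351 + 0.7026) = 0.68.

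**Step 4: log-rank error by simulation** (3,000 to 6,000 runs per scenario).

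| Share excluded (q) | Risk from day 0, no deaths: rate ratio; error | Risk from day 14, 15% mortality: rate ratio; error |
| --- | --- | --- |
| All | 0.63–0.64; 34–35% | 0.68; 28.6% |
| Half | 0.82–0.83; 10–11% | 0.84; 9.9% |
| Quarter | 0.92; 6.5–7% | not run |
| None | 1.00; 5% | 1.00; 6.0% (ITT in the same runs 6.0%) |

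At q = 1 essentially every rejection favours CCP. ITT error in the q = 1 runs from day 14 is 4.9%.

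**Step 5: sensitivity at q = 1, risk from day 14.**
- Mortality of 0, 5, 15 and 30% gives 28.1, 28.0, 28.6 and 27.2%. Mortality hardly matters; the gap between the two columns comes from the start of risk.
- The front-loaded hazard gives 45.2% (rate ratio 0.54).
- At 50% one-year infection the error is 12.8% with constant hazard and 22.5% with front-loaded hazard.
- If 30% enrol too late to receive all four infusions in window, it is 14.7% (rate ratio 0.73).
- If completion to 12 months is required in both arms, it is 24.2%.

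**Step 6: survival.** Suppose CCP deaths before day 90 leave the set and control deaths stay. At 15% mortality λ = −ln(0.85) = 0.1625. PP one-year survival is exp(−0.1625 × 275/365) = 88.5% for CCP against exp(−0.1625 × 351/365) = 85.5% for controls. The simulation gives 88.4% and 85.5%, and at 30% mortality 76.6% and 70.8%.

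**The case against.** The strongest objection is that the mechanism is not written down. Nothing in sections 4.4.1, 5.2 or 6.3 says that infection ends the infusions. If every infected participant continues, the rate ratio is 1.00 and the error matches ITT. A reader might infer that the definition necessarily removes early CCP infections; the text does not support that. It leaves the matter open, and the bias is conditional on it.

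Four further stronger readings also fail:
- *Controls face no condition at all.* They must also complete the planned procedures without major violations. Read strictly, that removes control deaths before 12 months, and the survival gap then vanishes. The infection bias does not (24.2% at q = 1).
- *Dropping early CCP deaths favours CCP on the primary endpoint.* With deaths censored it does not: at q = 0 the crude PP infection proportion is slightly higher with CCP (76.3% against 74.4%). The effect is on survival. If the infection-free survival named in section 5.3 counts death as an event, there is a small effect there (rate ratio 0.96 at 15% mortality, error about 6%).
- *Toxicity removes CCP participants by rule.* Section 6.3 says "If any Grade ≥3 adverse event occurs, the infusion is immediately discontinued", which stops the infusion in progress. It does not say whether later ones are given.
- *PP is set up to be the headline.* ITT is listed first, and section 5.4 uses it in the robustness comparison. PP is never given precedence; there is simply no ranking.

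Late enrolment can also pull the other way, as Step 5 shows. What stands is the one-sided day-90 requirement, combined with an endpoint clock that starts at transplantation.

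**Conclusion.** The PP definition is asymmetric in time, and following it as written can bias the PP infection comparison toward CCP. At the protocol's own 80% incidence and 36 per arm, with no true effect and constant hazard, the log-rank error is about 29–35% if all CCP participants infected before day 90 are excluded, about 10% if half are, and nominal if none are. It is higher if infections cluster early, and lower at lower incidence or with late entry. The decisive unknown is how many infected participants would miss an infusion, which the protocol does not settle. PP survival is flattered by about 3 percentage points at an assumed 15% mortality if control deaths are kept. ITT is untouched. This should be fixed, but it does not undermine the trial's main comparison provided ITT is named as that comparison.

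**What to change.** In the Study Summary and section 5.2, name ITT as the primary efficacy population and PP as supportive. In section 5.2, define CCP-arm adherence as receipt of every infusion that fell due before the earliest of first infection, death and the end of the fourth-infusion window. Infusions missed because of infection or death then exclude nobody, however infusions after infection are handled clinically. State also that, in either arm, infection or death before 12 months is not a failure to complete the planned procedures.

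A landmark at the end of the infusion period, applied to both arms, is not recommended. Applying the day-90 condition to both arms does restore the error to 5.0–5.8%, but it discards the infections that the infusions are meant to prevent and, if plasma works, conditions on an outcome that treatment affects.

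The cost is one reworded definition and one added sentence, with no extra patients or data. The PP result may look slightly less favourable to CCP.
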